### Study variables

This study investigates the effects of a Mentored Writing Retreat Programme (MWRP) as the independent variable on several dependent variables. These dependent variables encompass Knowledge, Attitude, Publication Efficacy, and Publication Status. Through analysing these variables, the study aims to understand the impact of MWRP on participants' knowledge, attitudes, efficacy in publishing, and their actual publication status, offering insights into the effectiveness of such programs in enhancing scholarly productivity and publication success among researchers.

Operational Definitions•Knowledge: Knowledge refers to the participants’ understanding of the research publication process, including manuscript preparation, journal selection, and submission procedures. Score range 0–30; higher scores indicate better knowledge.•Attitude: Attitude refers to the participants’ perceptions, beliefs, and disposition towards research publication and engagement in scholarly writing activities.Score range 24–120; higher scores indicate positive attitude.•Publication efficacy: Publication efficacy refers to the participants’ self-reported confidence in their ability to successfully prepare, submit, and publish a research manuscript in indexed journals.Score range 12–60; higher scores indicate higher confidence.•Publication status: Number of manuscripts completed/submitted/published.

### Description of the tool

All tools used were either adapted from validated instruments or developed by the researcher following standard tool development guidelines. Tools underwent content validation by seven subject experts in nursing education, research, and biostatistics, and a pilot test was conducted among 30 nurse researchers not included in the main study. Reliability was established using Cronbach’s alpha for internal consistency (Table 1).

**Table 1 tbl0001:** Description of the research tools.

Phase	Name of the Tool	Type of the Tool	Number of Items	Prepared	Cronbach’s Alpha
Phase 1					
Tool 1	Demographic Proforma		15 items	Researcher	
Tool 2	DiaZePam survey questionnaire on barriers of nurse researchers to research publication[23]	Semi-structured Questionnaire	15 items with sub-items.	Developed by French researchers and available in the public domain.	0.786
Tool 3	Interview guide to explore the barriers and facilitators of nurse researchers on research publication	Semi-structured questions	10 open-ended questions	Researcher	
Phase 2					
Tool 4	Knowledge of the research publication process of nurse researchers	Structured knowledge questionnaire	30 multiple choice questions	Researcher	0.809
Tool 5	Attitude of nurse researchers toward research publication	5-point Likert scale	24 statements.	Researcher	0.795
Tool 6	Publication efficacy of nurse researchers	Rating scale	12 items	Researcher	0.856
Tool 7	Publication status of nurse researchers	Checklist	8 Items	Researcher	

The DiaZePam survey questionnaire [23], originally developed by French researchers, was used to assess barriers to publication. Although not standardized for Indian settings, it was content-validated and culturally adapted before use. Modified items were pretested, and reliability (Cronbach’s α = 0.786) was confirmed for the adapted version.

### Procedure for data collection

Phase I will begin with a quantitative survey to identify perceived barriers and facilitators among 317 nurse researchers across Karnataka. Following the survey, Focus Group Discussions (FGDs) will be conducted, each lasting 45–60 min with 10–12 participants, to gain deeper insights into thematic barriers and enablers.

The results from Phase I will guide the development of a Research Publication Manual and the MWRP intervention.

### Research publication manual

A structured Research Publication Manual will be developed and used as a core resource in the Mentored Writing Retreat Programme (MWRP). It will be informed by Phase I findings, literature, and expert input to ensure contextual relevance (Table 2).

**Table 2 tbl0002:** Description of mentored writing retreat programme (MWRP).

Components	Major area/topic to be covered	Time (Theory)	Time (Practical)	Learning resources	Writing task
Workshop 1 Basic components of scientific writing and publication	Introduction and course orientation 1. Components of a scientific paper • Structured style • Abstract & title • Figures & tables • Citations 2. Preparing an article for publication	4 h	4 h	Research publication manual Hands-on session: research article preparation	Preparing a research article
	Mentoring and follow-up				
Workshop 2 Steps in research publication process	Appraisal of a scholarly article Selection of journals Manuscript preparation & submission Review process Final approval	4 h	4 h	Manuscript samples Hands-on session: manuscript preparation	Manuscript preparation
	Mentoring and follow-up				
Workshop 3 Publication specific information	Editorial management systems Publication ethics & misconduct Editorial policies and processes	4 h	4 h	Interactive lectures Resources for publication	Manuscript submission
	Mentoring and follow-up				

The manual will provide step-by-step guidance based on the IMRaD structure, covering development of the introduction, description of methods, presentation of results, and interpretation in discussion. It will also include sections on journal selection (scope, indexing, and avoiding predatory journals), publication ethics (authorship, plagiarism, and research integrity), and the manuscript submission process (cover letter preparation, submission systems, and responding to peer review).

Additionally, the manual will include practical tools such as checklists, templates, and sample formats to support manuscript development. It will be used during workshops and mentoring sessions.

In Phase II, eligible participants (*n* = 100) will be randomly assigned to either an intervention (*n* = 50) or a control group (*n* = 50). The intervention group will participate in the MWRP, comprising three workshops conducted over a four-month period. The control group will receive no intervention during this period. Pre- and post-assessments will be conducted for both groups at baseline, as well as at four- and six-month post-intervention.

All data will be coded anonymously, stored securely, and accessible only to the principal investigator.

Recruitment and Allocation Procedures.

Participants for Phase I will be recruited from nursing institutions across Karnataka through official communication with institutional heads and dissemination of study information via email and professional networks. Eligible nurse researchers who meet the inclusion criteria and provide informed consent will be enrolled in the survey. Participants for focus group discussions will be purposively selected from survey respondents to ensure diversity of experiences and perspectives.

For Phase II, participants will be recruited from Phase I respondents who indicate willingness to participate in the Mentored Writing Retreat Programme (MWRP) and meet the predefined eligibility criteria. After obtaining informed consent, eligible participants will be enrolled and assigned unique identification codes.

Given the quasi-experimental design, participants will be allocated into intervention and control groups using a non-randomized approach. Allocation will be based on feasibility and participant availability, ensuring comparable group sizes (*n* = 50 per group). Efforts will be made to maintain baseline comparability between groups by considering key characteristics such as academic qualification, prior publication experience, and institutional affiliation.

The intervention group will receive the MWRP, while the control group will continue with routine academic activities without structured intervention during the study period. To ensure ethical fairness, the control group will be provided access to the training materials after completion of the study.

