**Methods:**

A participatory action research design will be adopted and implemented in two phases. **Phase I** will examine publication barriers and facilitators through a survey and focus group discussions among nurse researchers across Karnataka (*n* = 317). **Phase II** will use a quasi-experimental pre-test–post-test design with intervention and control groups (*n* = 50 per group). The MWRP will be developed based on Phase I findings and will include structured workshops, mentoring, and guided manuscript development over four months, followed by structured follow-up after six months post-intervention.

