Barriers to publication are multifaceted. External challenges include limited funding, insufficient research infrastructure, high publication charges, and prolonged review times [20,21]. Internal barriers include lack of time, inadequate writing skills, and difficulty with academic English[22,23]. The availability of mentorship, technical guidance, and feedback mechanisms has been identified as a key facilitator for overcoming these obstacles[20,24]. Previous studies also highlight that although many nursing faculty members show positive attitudes toward research, confidence in writing and publishing remains limited [25,26].

These contextual factors indicate the need for structured, practical, and accessible scientific writing support models for academic nurses. Short-term, focused writing programmes may offer an efficient approach for researchers who cannot participate in long-duration research courses[27]. This protocol is situated within this broader context. It outlines a structured approach to exploring publication challenges among nurse researchers and describes the development of a Mentored Writing Retreat Programme designed to address skill-based needs through a participatory, capacity-building process.

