**Fig. 1 fig0001:**
[figure not shown]
Framework of MWRP.

The development and implementation of the MWRP will follow four iterative PAR cycles:•Plan: Identification of barriers and facilitators through surveys and focus group discussions.•Act: Development and implementation of the MWRP and research publication manual.•Observe: Monitoring participant progress, engagement, and outcomes during workshops and mentoring.•Reflect: Evaluation of feedback from participants and mentors to refine workshop content, mentoring strategies, and delivery methods.

Each cycle will inform subsequent modifications, ensuring that the programme remains contextually relevant, responsive to participant needs, and continuously improved.

*Phase 1: Exploratory Survey on Barriers and Facilitators for Research Publication.*

Phase I of the study is structured as an explorative investigation aiming to identify the barriers and facilitators for research publication as perceived by nursing professionals employed in nursing institutions. This phase employs a combination of methods, including a descriptive survey and focus group discussions.

The primary objective of Phase I is to gain insights into the challenges and supportive factors encountered by nursing professionals in the process of publishing research findings. Through the descriptive survey, participants will provide valuable information regarding their experiences, perceptions, and the various obstacles hindering or facilitating their engagement in research publication activities.

Additionally, focus group discussions will be conducted to delve deeper into the identified themes and gather rich qualitative data. These discussions will offer a platform for participants to express their perspectives, share experiences, and offer suggestions for overcoming barriers to research publication.

The findings from Phase I will serve as a foundation for informing the development and implementation of interventions aimed at enhancing the research publication process among nurse researchers.

*Phase 2: Impact of Mentored Writing Retreat Programme (MWRP).*

In Phase II, the study shifts focus towards evaluating the impact of the Mentored Writing Retreat Programme (MWRP) on optimizing the research publication process among nurse researchers. This phase adopts a quasi-experimental design, specifically employing a Pretest-Posttest approach with both control and interventional groups.

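### Phase II allocation is described both as random and as non-random by availability; the statements must be reconciled, and allocation by availability could bias publication status

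*Protocol article*

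**What the plan says.** Two statements on Phase II allocation stand a few paragraphs apart in the Protocol article.

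- In the text after Table 2 (section Research publication manual), eligible participants, 100 in all, "will be randomly assigned to either an intervention" group of 50 or a control group of 50.
- Under Recruitment and Allocation Procedures, "participants will be allocated into intervention and control groups using a non-randomized approach". The rule follows: "Allocation will be based on feasibility and participant availability, ensuring comparable group sizes". Comparability at baseline is to be sought by "considering key characteristics such as academic qualification, prior publication experience, and institutional affiliation".

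The rest of the article uses the second description. In the abstract, Phase II "will use a quasi-experimental pre-test–post-test design with intervention and control groups". The Phase 2 description under Design framework says: "This phase adopts a quasi-experimental design, specifically employing a Pretest-Posttest approach with both control and interventional groups". The Specifications table and Limitations also call the design quasi-experimental.

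On time as a factor, the Background states: "Internal barriers include lack of time, inadequate writing skills, and difficulty with academic English". Limitations adds that completing manuscript tasks may vary with workload and competing duties.

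**The concern.** The allocation method decides how a difference between the groups may be read. Under randomisation, baseline differences are due to chance and the test accounts for them. Under allocation by availability they may be systematic, and the p-value does not cover them. A reader or replicator cannot tell from this article which method applies. A later report could describe the trial as randomised on the strength of one sentence.

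The non-random rule also raises a concern of its own. Availability matters far more for one arm than for the other, because the programme takes time and the control condition does not. Time is a factor that the protocol itself associates with publishing. If availability steers who enters the intervention arm, part of any difference in manuscripts completed, submitted or published could reflect free time and not the programme.

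**Working it through.** No sample-size, power or alpha figure in the protocol is at stake here, so there is no stated figure to reproduce. The check compares the text and adds one illustration.

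**1. Can both allocation statements hold?** They concern the same 100 people, the same two arms and the same 50/50 split. One says random. The other says non-random and names feasibility and availability as the basis. They exclude each other.

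**2. Which is the outlier?** Abstract, Specifications table, Phase 2 description and Limitations all say quasi-experimental. The dedicated allocation paragraph gives that design as its reason for not randomising. Random assignment appears once and is the outlier. No sentence withdraws it.

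**3. Does availability bear unequally on the arms?**
- Intervention: three workshops of 8 hours, 3 × 8 = 24 hours, plus bi-weekly mentoring of 30–60 minutes per session (Programme structure and timeline; Mentoring structure and follow-up).
- Control: usual academic work with no structured programme.

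Only the first arm needs participants who can free up this time. The rule would therefore tend to place people with more free time there. This is an inference from the demands of the arms; the protocol does not state it.

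**4. Is available time linked to an outcome?** Background lists lack of time as a barrier to publication, and Limitations ties task completion to workload. Publication status is defined by manuscripts completed, submitted or published (Study variables). The link is direct for that outcome. For knowledge, attitude and efficacy the protocol offers no comparable statement.

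**5. Do the stated safeguards capture it?**
- The characteristics named for comparability are qualification, publication record and institution. Time and workload are not among them, although the list is open.
- In Data analysis, the repeated measures ANOVA controls for baseline values. A pre-test score or earlier publication status does not measure time available during the study.
- Publication status is assigned to the Cochran Q test and to before–after t-tests, with no covariate adjustment described.
- Limitations mentions external factors in general and does not mention the allocation rule.

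**6. How much could it matter?** The documents give no size for the imbalance. As an assumption, let allocation shift the outcome by b standard deviations when the programme has no effect, and let a two-sided 5% z-test compare 50 per group without adjustment for available time. The rejection rate is P(|Z + b·√(n/2)| > 1.96), with √(50/2) = 5.

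| Assumed b (SD) | b × 5 | Rejection rate |
|---|---|---|
| 0 | 0 | 5% |
| 0.1 | 0.5 | 8% |
| 0.2 | 1.0 | 17% |
| 0.3 | 1.5 | 32% |
| 0.5 | 2.5 | 71% |

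The table shows how sensitive the error rate is to an imbalance of this kind. It does not estimate the bias in this trial.

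**The case against.** The strongest reply is that the intended design is clear. The article says quasi-experimental throughout, the allocation paragraph is explicit, and random assignment may be a drafting slip that one deletion cures. On this view, asking for a randomised trial replaces a declared design with a reviewer's preference. Most of this stands, and it is why reconciling the text comes first and randomisation is only an option. The slip still has to be corrected, because it changes what the group comparison means.

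Several points also limit the bias argument:
- A reader might infer that the rule puts people with time to write into the intervention arm. The protocol does not say so. Availability could mean workshop dates, travel or site logistics, and being free on three days is only a proxy for writing time.
- A reader might infer that availability directly causes the outcome. The Background lists lack of time as one barrier among several, so the protocol supports a link and no more.
- Both arms come from people willing to join the programme, to publish and to be mentored. This narrows the contrast between arms without removing it.
- The comparability list is illustrative, baseline publication status is measured, and Limitations concedes that the design may leave external factors uncontrolled and that task completion depends on workload.

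These points reduce the likely bias. They do not resolve the contradiction, and none of them provides for measuring available time.

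**Conclusion.** The contradiction is certain and rests on the text alone: the same participants are said to be randomised and not randomised. It must be corrected, because it decides whether the comparison can be read as randomised.

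The bias concern holds in a limited form. Allocation by availability would tend to favour the intervention arm in free time, and the safeguards as described do not capture that. Publication status is the outcome most exposed. This assumes that availability is judged against the programme's demands and that free time helps people finish manuscripts. The first is inferred; the second has support in Background and Limitations. The size is unknown. Any figure in percentage points would need submission rates by available time, which the protocol does not give.

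The documents do not support the stronger conclusions that the group comparison is uninterpretable or that only a randomised design would do. A controlled pre–post comparison with its limits stated can still support a qualified estimate of effect.

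**What to change.** First, reconcile the two statements so that the article, the registration and the ethics text describe one allocation method.

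**If allocation has been or will be non-random:**
- Remove the statement of random assignment.
- Record available time or workload at baseline for all 100 participants.
- Adjust the between-group comparisons, including publication status, for it and for qualification, prior publication and institution.
- Name allocation by availability as a limitation, and qualify causal conclusions accordingly.

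This costs a text correction, one or two baseline questions and a few covariates. If the baseline has passed, time or workload can only be asked in retrospect, and the report should say so. With 50 per group, institution may need to be grouped.

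**If allocation has not yet happened,** the sponsor could instead require availability for the workshop dates from all 100 participants, randomise 1:1 after the pre-test, stratified by prior publication and qualification, and drop the availability rule. Consent and identification codes already precede allocation. The downside is that people who cannot make the dates are excluded, and the registration and ethics text must be aligned. Colleagues at one institution could also share the manual across arms.

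The second route may already be closed: the Sample size section reports the inclusion of the 100 participants in the past tense, although other sections use the future. The sponsor should state which situation applies.

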### Description of the intervention-mentored writing retreat programme (MWRP)

MWRP is a learning concept developed by the researcher to optimize the research publication of nurse researchers based on a participatory action research approach. Participatory action research emphasizes the involvement of participants throughout the study process.

The MWRP combines workshops, mentorship support, self-learning resources, interactive learning, and follow-up to support participants in preparing and submitting manuscripts to indexed journals.

Three workshop sessions will be conducted over a four-month period at various intervals, with follow-up to be conducted after six months. So, the total duration of the programme will be ten months. Participants will engage in comprehensive sessions covering the basic components of scientific writing and editing, including lectures, presentations, hands-on sessions, and feedback. Topics include Introduction and course orientation, Components of a scientific paper structure & style, Abstract & title, Figures & tables, Citations, and Preparing an article for publication. Additionally, steps in the research publication process will be explored, involving lectures, presentations, hands-on sessions, and feedback to develop skills in scientific article appraisal, journal selection, manuscript preparation & submission, the review process, and final manuscript approval. Furthermore, publication-specific information will be provided through interactive lectures, presentations, and feedback sessions, covering various terminologies such as peer review, journal indexing, impact indicators, editorial management systems, publication ethics & misconduct, and editorial policies and processes.

### Programme structure and timeline

The MWRP will be implemented over a 10-month period, comprising three workshops conducted over four months, followed by structured mentoring and follow-up:•Month 1 (Week 1): Workshop 1 (8 h) - Introduction to scientific writing, manuscript structure, title and abstract development.•Month 2 (Week 5): Workshop 2 (8 h) - Writing the introduction and methods, literature synthesis.•Month 4 (Week 12): Workshop 3 (8 h) - Results, discussion, journal selection, and manuscript submission.•Months 1–10: Bi-weekly mentoring sessions.•Month 5: Post-test assessment (knowledge, attitude, efficacy).•Month 10: Follow-up assessment (publication status).

Rationale: The spacing between workshops allows participants sufficient time to complete writing tasks, receive feedback, and iteratively improve their manuscripts.

